### Selection Criteria

The inclusion criteria are patients undergoing breast reconstruction at WCH. They must be able to use a mobile device and communicate in English. The exclusion criterion are (1) patients who are smokers, because smokers carry increased rates of complication and both surgeons have a policy to solely operate on non-smokers (minimum smoke-free period of 1 month leading to surgery). Patients must not (2) suffer from chronic pain, (3) be taking narcotic (morphine-like) medication for pain on a regular basis, and (4) have an allergy to local anesthetics or morphine-like medications. Pain ratings captured in the VAS and QoR-9 are important for judging quality of postoperative recovery. Pre-existing pain or an inability to take narcotics would compromise the reliability of these measures.

Patients with hearing or speaking impairments will be accommodated with the help of translators. The person who regularly attends visits with the patient will facilitate this, or if no such person is available, we will use a hospital translator. All patients will receive an explanation of the study and the consent form in writing. All material will be understandable by patients with a grade 6 reading level. If our patients have lower than a grade 6 reading level, we will ask them if there is a family member at home who could assist them with the use of the mobile device.

### Intervention

Eligible patients will be randomized in equal proportions (1:1) between mobile app and in-person follow-up care. All patients will receive what is currently the medical standard of care in this hospital. Patients in the conventional follow-up group will have a planned clinic follow-up at 4 weeks postoperative. This is the follow-up schedule currently used by both surgeons. At these scheduled follow-ups, patients will be asked to complete the VAS to assess pain and the QoR-9.

The mobile app follow-up group will have no planned in-person follow-up at 1 week and 4 weeks postoperative. However, these visits will be replaced with surgical site examination via submitted photos, VAS, and QoR-9 questionnaire monitoring. All of this information is submitted via the mobile app (QoC Health Inc, Toronto). Patient reporting will begin following discharge from the recovery room. Since 75% of complications occur within the first 2 weeks of discharge [21], we will use daily monitoring for 2 weeks and then weekly monitoring for 4 weeks. The data entered through the mobile phone app will reach a double-encrypted server. The surgeon will then use a wireless interface to access that data and monitor the patient’s condition (not in real time). High pain scores will be flagged in the database for quick viewing. Any red flags will prompt in-person follow-up. Physicians will summarize the clinical findings recorded by the mobile app at 1 week and 4 weeks postoperative using the prototypical subjective, objective, assessment, and plan (SOAP) note.

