#### Why Use the QoC Health Inc Mobile App?

The QoC Health Inc mobile app allows patients to submit photos and answers to a validated quality of recovery (QoR) questionnaire and Visual Analog Scale (VAS) for the first 30 days postoperative using their mobile device [19]. A feasibility study, including 30 breast reconstruction patients, showed once daily reporting was well tolerated even in the first week postoperative period. There were high levels of satisfaction with the mobile device and app (3.9/5) and low levels of anxiety in knowing that their surgeon was monitoring their recovery [6]. One wound infection and one early dehiscence was picked up using the mobile phone app, leading to immediate intervention. Surgeons were able to follow patient reports on a Web portal. Post-pilot surveys reported an overall positive experience. All patients attended the standard in-person follow-up care visit at 1 and 4 weeks postoperative. Surgeons felt that at least one early follow-up clinic visit could be eliminated when using the remote monitoring technology. This was an unexpected finding [6].

The following proposed catalyst study builds on this pre-existing data by actually eliminating one or more in-person postoperative follow-ups and performs a cost-effectiveness assessment. Demonstrating cost-effectiveness in an elective ambulatory postoperative population would promote its use in similar surgical settings.

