### Secondary Outcomes

The total number of health care telephone calls and emails (including specialist, family physician, and emergency department) related to the surgery will be captured at 4 weeks after surgery.

We will also record and report all complications occurring within the 30-day period. This was chosen based on literature surrounding postoperative complications in the first 30 days [21]. This will be captured at 4 weeks after surgery. The complication rate within this patient population is 4%, with 1% rate of reoperation. The most common complications are superficial skin infections managed with a short course of oral antibiotics. In the pilot study, all (1/30) superficial skin infections were picked up by the mobile phone app and antibiotic prescriptions were called in to the patient’s local pharmacy [6]. Rare non-serious complications include seromas and wound dehiscence. All wound dehiscence (1/30) were picked up by the app in the pilot study. These both warrant a trial of conservative (watch-and-wait) therapy. After failed conservative therapy, seroma may be drained via ultrasound guided needle aspiration. Wound dehiscence may require surgical management under local anesthetic in the clinic or, if more involved, under regional anesthetic in the operating room. Rare and potentially serious complications include hematomas. If a hematoma is small and non-expanding, it can be managed conservatively (watch-and-wait). If it is larger and expanding, it may require urgent (<24 hours) evacuation in the operating room. This type of urgent situation presents to the emergency department, not to a clinic visit.

There is no potential for clinical compromise in the telemedicine group. If anything, superficial skin infections may be identified and treated earlier. Any study participant can schedule a face-to-face postoperative visit with the surgeon at any time; however it is anticipated that the mobile phone follow-up care will eliminate the need for one or more clinic visits. Devices may be returned to the clinic in-person or by standard mail.

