### Sample Size

The average breast reconstruction patient attends two in-person follow-up visits within the first month after surgery. If we assume that we can avert at least one in-person visit in the mobile app arm and that we have equal number of participants in both groups, we can use the E-test for count data to generate a sample size of 64 (32 patients per group) at a power of 95% (*P*=.05). The E-test is more robust and more powerful than the Conditional test (C-test) originally described to compare two counts. If we assume a 10% dropout rate, we will increase our sample size target to 36 patients per group.

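### The control arm is given one planned visit (week 4), while the app-arm text, the pilot description and the sample size imply two (weeks 1 and 4)

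*Protocol article*

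**What the plan says.** In the protocol article, Methods, Intervention, the control arm is defined by this sentence: "Patients in the conventional follow-up group will have a planned clinic follow-up at 4 weeks postoperative". The article adds that both surgeons already work to this schedule. The next sentence turns to the plural: "At these scheduled follow-ups, patients will be asked to complete the VAS to assess pain and the QoR-9". The following paragraph defines the other arm: "The mobile app follow-up group will have no planned in-person follow-up at 1 week and 4 weeks postoperative". It goes on to say that photographs, the pain scale and the recovery questionnaire replace those visits, and it sets physician summary notes at the same two time points.

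Two other sections bear on the schedule:

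- Why Use the QoC Health Inc Mobile App?, on the pilot: "All patients attended the standard in-person follow-up care visit at 1 and 4 weeks postoperative".
- Sample Size: "The average breast reconstruction patient attends two in-person follow-up visits within the first month after surgery". The effect follows from it: "If we assume that we can avert at least one in-person visit in the mobile app arm".

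Unscheduled visits are open to both arms. Under Secondary Outcomes: "Any study participant can schedule a face-to-face postoperative visit with the surgeon at any time".

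On app reporting, the Intervention section says "we will use daily monitoring for 2 weeks and then weekly monitoring for 4 weeks". The Abstract instead has weekly reports for two weeks after the daily phase, and the Timeline section limits participation to one month after surgery.

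**The concern.** The app cannot replace a week-1 visit that the comparator does not have. Read literally, the control sentence plans one visit against none. Read with the rest of the article, the plan is two visits against none, with an expected mean of about 2 against 1 once visits that still take place are counted.

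The difference matters because the primary outcome is a count of surgery-related physician visits. Planned control visits enter that count directly and largely set the control mean. They also enter the in-person side of the cost comparison. Anyone who schedules control patients from the sentence as written would leave out week 1, and the trial would depart from the assumption on which it was sized. A reader cannot tell whether the trial tests replacing one visit or two.

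**Working it through.** **1. The statements side by side (protocol article)**

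| Place | Control or standard in-person visits implied |
|---|---|
| Intervention, control sentence | 1 (week 4) |
| Intervention, next sentence | more than one (plural) |
| Intervention, app-arm paragraph | 2 (weeks 1 and 4) replaced |
| Why Use the QoC Health Inc Mobile App? | 2 (weeks 1 and 4), called standard |
| Sample Size | mean of 2 in the first month; weeks not named |

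The control sentence is the only one that names a week-4-only schedule.

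**2. Reproducing the stated sample size**

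Inputs from the Sample Size section: control mean 2, app mean 2 − 1 = 1, equal arms, alpha 0.05 (sidedness not stated), power 95%, 32 per group, 10% dropout.

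E-test: let X₁ and X₂ be the total visits in two arms of n patients each. The statistic is T = (X₁ − X₂)/√(X₁ + X₂). Its p-value is computed with both totals taken as Poisson with mean (X₁ + X₂)/2. Power is the Poisson probability, under the true totals nλ₁ and nλ₂, of all outcomes with p ≤ 0.05, by full enumeration.

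- One-sided, n = 32: power 0.952. With n = 31 it is 0.947, so 32 is the smallest n that reaches 95%.
- Two-sided, n = 32: power 0.911. Reaching 95% takes 39 per group.
- Normal-approximation check, n = (z_α + z_β)²(λ₁ + λ₂)/(λ₁ − λ₂)²: one-sided (1.645 + 1.645)² × 3/1 ≈ 32.5; two-sided (1.960 + 1.645)² × 3/1 ≈ 39.0.
- Dropout: 32/0.9 = 35.6, rounded up to 36 per group, 72 in all. This matches.

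The stated figure is therefore reproduced by a control mean of 2 and an app mean of 1, tested one-sided.

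**3. If a single control visit were really intended**

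The article gives no rate of unscheduled visits, so every mean below except 2 vs 1 is an assumption. E-test, 32 analysed per arm, alpha 0.05:

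| Control vs app mean | Power, two-sided | Power, one-sided |
|---|---|---|
| 2 vs 1 (as sized) | 91.1% | 95.2% |
| 1 vs 0.5 | 64.4% | 75.4% |
| 1.25 vs 0.5 | 90.6% | 94.9% |
| 1.5 vs 0.5 | 98.5% | 99.4% |
| 1.25 vs 0.25 | 99.9% | 99.9% |

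Nearer to the literal one against none, two-sided power is 97.9% at 1 vs 0.25 and above 99.9% at 1 vs 0.1. Power can therefore fall below the planned level or rise above it, depending on how many app patients still come in.

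**4. The monitoring period**

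- Abstract: 14 daily + 2 weekly = 16 reports, the last on day 14 + 2 × 7 = 28.
- Intervention: 14 daily + 4 weekly = 18 reports, the last on day 14 + 4 × 7 = 42. The final two (days 35 and 42) fall outside the 30-day outcome window and the one month of participation.

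**The case against.** The strongest reply is that this is a dropped phrase with no numerical consequence. The intended schedule can be worked out from the plural, the app-arm paragraph and the pilot text, and once week 1 is restored nothing in the design, analysis or sample size changes. The control arm is also tied to the existing practice of two surgeons at one centre, who are unlikely to book visits from a journal article. Much of this is fair. The point is a correction of wording, and harm in practice is possible but not shown. It is still more than a matter of style, because the sentence defines the comparator for an outcome that counts visits, and it presents the one-visit schedule as current practice.

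The Sample Size section gives an average of visits attended, which one planned visit plus extra visits could also produce. That is right, and the section alone would not settle the matter. It would not explain the app-arm paragraph or the pilot text, both of which name weeks 1 and 4. The data collection sections mention only a week-4 assessment in the control arm, but that is compatible with either schedule.

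The one clearly low power figure, 1 vs 0.5, comes from halving the absolute effect. If a full visit is still averted from a lower control mean, power rises. This stands, and it is why no loss of power is claimed here.

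The monitoring period is a separate matter from control visits. It is real but secondary, and adds nothing to the weight of the main point.

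**Conclusion.** The concern holds. The control sentence contradicts the app-arm text of its own section and the pilot description, and it does not fit the sample size assumption. The most probable cause is that week 1 was omitted, although the article cannot prove which statement is wrong.

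On the two-visit reading the numerical effect is nil: 2 vs 1, 32 per arm and 72 in total all stand. On the one-visit reading the sample size has no stated basis, and two-sided power at 32 per arm could lie anywhere from about 64% to above 99%, under assumed means that the article does not supply. The inconsistency should be fixed because it concerns the comparator and the primary outcome. Separately, 32 per arm gives 95% power only with a one-sided test, and the article does not state the sidedness.

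**What to change.** Confirm the control schedule with the two surgeons, then amend the control sentence in the Intervention section to planned clinic visits at 1 week and 4 weeks. The sample size then needs no change.

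Only if a single week-4 visit is truly intended should the other places change instead. In that case, correct the plural and the app-arm paragraph in Intervention and the description of standard visits in the pilot section. In Sample Size, restate both assumed means, including unscheduled visits, and recompute the power.

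In the same edit, change the app reporting period in Intervention to daily for two weeks and then weekly for the following two, in line with the Abstract and the Timeline section.

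The cost is two wording corrections in one section, with no added patients if the two-visit schedule is confirmed.

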### Primary Outcome

The total number of physician visits (including specialist, family physician, and emergency department) related to the surgery. These data will be captured at 4 weeks after surgery.

### Secondary Outcomes

The total number of health care telephone calls and emails (including specialist, family physician, and emergency department) related to the surgery will be captured at 4 weeks after surgery.

We will also record and report all complications occurring within the 30-day period. This was chosen based on literature surrounding postoperative complications in the first 30 days [21]. This will be captured at 4 weeks after surgery. The complication rate within this patient population is 4%, with 1% rate of reoperation. The most common complications are superficial skin infections managed with a short course of oral antibiotics. In the pilot study, all (1/30) superficial skin infections were picked up by the mobile phone app and antibiotic prescriptions were called in to the patient’s local pharmacy [6]. Rare non-serious complications include seromas and wound dehiscence. All wound dehiscence (1/30) were picked up by the app in the pilot study. These both warrant a trial of conservative (watch-and-wait) therapy. After failed conservative therapy, seroma may be drained via ultrasound guided needle aspiration. Wound dehiscence may require surgical management under local anesthetic in the clinic or, if more involved, under regional anesthetic in the operating room. Rare and potentially serious complications include hematomas. If a hematoma is small and non-expanding, it can be managed conservatively (watch-and-wait). If it is larger and expanding, it may require urgent (<24 hours) evacuation in the operating room. This type of urgent situation presents to the emergency department, not to a clinic visit.

There is no potential for clinical compromise in the telemedicine group. If anything, superficial skin infections may be identified and treated earlier. Any study participant can schedule a face-to-face postoperative visit with the surgeon at any time; however it is anticipated that the mobile phone follow-up care will eliminate the need for one or more clinic visits. Devices may be returned to the clinic in-person or by standard mail.

A societal perspective will be adopted wherein all costs are assessed irrespective of the payer [22]. This perspective was chosen based on the US Panel on Cost-Effectiveness in Health and Medicine recommendations. This recommendation is meant to improve comparability and consistency across studies [23]. Furthermore, while a broad societal perspective will be adopted, results will also be presented using a narrower health system perspective that may be of key interest to health administrators and policy decision makers. This alternative perspective focuses on costs borne within the health system and excludes external costs as well as costs borne by patients and their caregivers.

Currently, there are no validated questionnaires that capture patient satisfaction with postoperative care. We have created a post-pilot survey that captures patient satisfaction with the care and information received. All answers are recorded using a 5-point Likert scale (Multimedia Appendix 1). We will also use the QoR-9 scores and VAS recorded at 4 weeks postoperative. Psychometric properties of the QoR-9 include convergent validity and discriminant construct validity. There is also good interrater agreement and internal consistency [24]. The test-retest reliability was 0.61 (*P*<.001). The preferred cut-off is 0.7; however, the QoR-9 was still favored over the QoR-40 due to its ease of use (<2 minutes required to complete the survey) [24].

### Sample Size

The average breast reconstruction patient attends two in-person follow-up visits within the first month after surgery. If we assume that we can avert at least one in-person visit in the mobile app arm and that we have equal number of participants in both groups, we can use the E-test for count data to generate a sample size of 64 (32 patients per group) at a power of 95% (*P*=.05). The E-test is more robust and more powerful than the Conditional test (C-test) originally described to compare two counts. If we assume a 10% dropout rate, we will increase our sample size target to 36 patients per group.

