**Results:**

A sample of 72 (36 patients per group) will provide an E-test for count data with a power of 95% (*P*=.05) to detect a difference of 1 visit between groups, assuming a 10% drop out rate. Count variables will be analyzed using Poisson regression. Categorical variables will be tested using a chi-square test. Cost-effectiveness will be analyzed using net benefit regression. Outcomes will be assessed over the first 30 days following surgery.

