### Poisson Regression

We will use person-level Poisson regression to determine if there is a difference in the number of visits attended between patients in the mobile app and in-person follow-up arm.

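### The 95% power claimed for 32 patients per group belongs to a one-sided 5% E-test; read as two-sided, the same design has 91%.

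*Protocol article*

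**What the plan says.** The Sample Size section takes the control mean from usual practice: "The average breast reconstruction patient attends two in-person follow-up visits within the first month after surgery". It assumes the trial can "avert at least one in-person visit in the mobile app arm", with groups of equal size. It then applies the E-test "to generate a sample size of 64 (32 patients per group) at a power of 95" per cent, with P=.05, and raises the target to 36 per group for 10% dropout.

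The Results paragraph of the abstract repeats the claim for the inflated sample: "A sample of 72 (36 patients per group) will provide an E-test for count data with a power of 95" per cent, again with P=.05, "to detect a difference of 1 visit between groups, assuming a 10% drop out rate".

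The Poisson Regression section names the analysis of visits as a person-level Poisson regression "to determine if there is a difference in the number of visits attended" between the arms. The Design Overview calls the trial a superiority trial. Nowhere does the article say whether the 0.05 is one-sided or two-sided.

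**The concern.** A P=.05 given without qualification, next to an analysis that looks for a difference, is ordinarily read as a two-sided 5% test. If the sample size was in fact worked out one-sided, the stated power does not belong to the comparison that the article describes.

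Power is a headline property of the design. It tells readers how much weight a non-significant result can bear. If it is overstated, the risk of missing a true reduction of one visit is larger than the article says.

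**Working it through.** **Inputs, all from the protocol article**

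- Control mean: 2 visits per patient in the first month (Sample Size).
- App-arm mean: 2 − 1 = 1 visit (Sample Size; the abstract gives the same difference of 1).
- Allocation: 1:1 (Intervention, Sample Size).
- Test: E-test for two Poisson counts (Sample Size).
- Level: 0.05, sides not stated.
- Stated result: 32 per group, 95% power.

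**Method**

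With n per group, the total visit counts are K1 ~ Poisson(2n) and K2 ~ Poisson(n). At n = 32 these have means 64 and 32. The test statistic is T = (K1 − K2) / √(K1 + K2). The E-test takes its p-value from the distribution of T when both totals are Poisson with the pooled mean (K1 + K2)/2. Power is the exact probability, summed over all (K1, K2), that this p-value is at most 0.05.

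**Step 1: reproduce the stated figure.** The dropout step is correct: 32/0.9 = 35.6, rounded up to 36. The power figure reproduces under one setting only:

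| n analysed per group | E-test power, one-sided 0.05 | E-test power, two-sided 0.05 |
|---|---|---|
| 31 | 94.7% | 90.3% |
| 32 | **95.2%** | **91.1%** |
| 36 | 96.9% | 93.9% |
| 38 | 97.5% | 94.95% |
| 39 | 97.8% | 95.4% |

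One-sided, 32 is the smallest n that reaches 95%, which is exactly the stated size. Two-sided, the smallest is 39.

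**Step 2: check by hand with the normal approximation.** The difference in means is 1, and its standard error is √((2 + 1)/32) = 0.306, so the standardized difference is 1/0.306 = 3.266.

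- One-sided: Φ(3.266 − 1.645) = Φ(1.621) = 94.7%.
- Two-sided: Φ(3.266 − 1.960) = Φ(1.306) = 90.4%.

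The gap of about 4 points comes from the choice of sides, not from details of the E-test.

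**Step 3: check the analysis that is planned.** For a Poisson regression on arm alone with 32 per group, exact two-sided power at 0.05 is 90.9% (Wald), 91.2% (likelihood ratio) and 91.2% (score). The named analysis therefore has about 91% power as well.

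**Step 4: size of the discrepancy.** The type II error is 100 − 91.1 = 8.9% against the stated 5%, or 1.8 times as large. If nobody drops out and all 36 per group are analysed, two-sided power is 93.9%, so 95% is not reached in that case either.

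**The case against.** The strongest reply is that nothing was miscalculated. The 95% reproduces exactly one-sided, the article never says two-sided, and some of its language has a direction: a superiority design, visits to be averted, a hope that the app will reduce in-person visits. A one-sided calculation may have been intended, and a fuller protocol or analysis plan that is not shown may say so.

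Part of this stands. The calculation is sound on its own terms; the fault is an undeclared one-sided level behind a comparison worded without direction. The two-sided reading is an inference from that wording and from convention. But superiority and the hoped-for direction describe the hypothesis and do not fix the level of the test. A one-sided 5% level is a material choice and has to be declared wherever the power is quoted. An increase in visits is also possible, because red flags in the app prompt in-person visits and the primary outcome counts family physician and emergency visits. Even if another document specifies a one-sided test, the two statements in the article cannot be interpreted without it.

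A second reply is that a gap of 3.9 points is small beside the uncertainty of the inputs. This is true. The assumption is at least one visit averted; with an app-arm mean of 0.95, two-sided power at 32 per group is about 94%, and with 0.90 it is 96.1%. Overdispersed counts would lower power. This limits the practical weight of the point, but it does not make 95% the right figure for the means of 2 and 1 on which the article bases it.

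**Conclusion.** The point holds. With the article's own inputs, 95% power at 32 per group is the power of a one-sided 5% E-test. The two-sided 5% comparison that the wording implies has 91.1% with 32 analysed per group and 93.9% with 36.

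This rests on three assumptions: Poisson variation in visit counts, exactly one visit averted, and P=.05 read as two-sided because no one-sided test is declared. The numbers are firm. The sidedness is a reading of the text, though the usual one. The consequence is modest: a design figure is overstated by about 4 points, while the trial keeps more than 90% power and remains adequately sized.

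**What to change.** In the Sample Size section and in the Results paragraph of the abstract, state that the test is two-sided at 0.05. Give power as 91% with 32 analysed per group, or 94% if all 36 are analysed, for means of 2 and 1 visits under Poisson variation. Say in the Poisson Regression section that the test is two-sided. The only cost is a slightly less favourable stated figure; recruitment does not change.

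If 95% two-sided power is wanted, it takes 39 analysed per group. With 10% dropout that is 39/0.9 = 43.3, so 44 per group and 88 in total, or 16 more than the planned 72. The result does not require this, since 91% is adequate. If a one-sided 5% test was truly intended, both power statements and the analysis section should say so and justify it.
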